## Abstract

**Background:**

Polyunsaturated fatty acid (PUFA) metabolism abnormalities have been long implicated in the etiology of schizophrenia. Although several randomized clinical trials have been carried out to assess the efficacy of omega-3 PUFA as add-on therapy in reducing psychopathology in populations of chronic patients with schizophrenia, only a few concern first-episode schizophrenia. The majority of these studies used a 12-week intervention based on ethyl-eicosapentaenoic acid (ethyl-EPA), however, with conflicting results. An intervention based on docosahexaenoic acid plus EPA has not been used in first-episode schizophrenia studies so far. No add-on supplementation studies have been carried out in medicated first-episode schizophrenia patients to assess the efficacy of omega-3 PUFA in preventing relapses.

**Methods:**

A randomized placebo-controlled one-center trial will be used to compare the efficacy of 26-week intervention, composed of either 1320 mg/day of EPA and 880 mg/day of DHA, or olive oil placebo with regard to symptom severity and relapse rate in first-episode schizophrenia patients. Eighty-two patients (aged 16–35) will be recruited for the study. Eligible patients will be randomly allocated to one of two intervention arms: an active arm or a placebo arm (olive oil). The primary outcome measure of the clinical evaluation is schizophrenia symptom severity measured by the Positive and Negative Syndrome Scale (PANSS). Other outcomes include depressive symptoms, patient functioning and the level of insight. Correlates of change measured during the study will include structural brain changes, oxidative stress and defense, as well as neuroplasticity indicators. Metabolic syndrome components will also be assessed throughout the study.

**Discussion:**

By comparing 26-week administration of EPA + DHA or (placebo) olive oil as add-on therapy in reducing symptom severity and one-year relapse rate in patients with first episode schizophrenia, it is intended to provide new insights into the efficacy of omega-3 PUFA and correlates of change, and contribute to the improvement of mental health care for individuals suffering from schizophrenia.

**Trial registration:**

This study has been registered at Clinical Trials.gov with the following number: NCT02210962.

## Background

### Polyunsaturated fatty acids in schizophrenia

Schizophrenia is a neurodevelopmental and neurodegenerative disorder displaying disturbance in multiple neurotransmission pathways. Since polyunsaturated fatty acids (PUFA) are essential for normal neurodevelopment, disturbances of PUFA metabolism may be involved in the etiology of neurodevelopmental disorders like schizophrenia [1]. PUFA are the major constituents of cell membrane phospholipids and take part in numerous biological processes including receptor binding, neurotransmission, signal transduction and the synthesis of active metabolites (i.e. eicosanoids), which control inflammation, oxidative stress and defense processes, among others. PUFA are abundant in the central nervous system, where they are the main constituents of neuronal membrane phospholipids. Long-chain PUFA, i.e. docosahexaenoic acid (DHA) and arachidonic acid (AA) are incorporated in Sn-2 position of phospholipids. DHA and AA are released from membrane phospholipids by phospholipase A2, and their derivatives take part in neuronal impulse transmission. Neuronal membranes are rich in DHA, which is essential for normal brain development [2]. The DHA/AA (n-3/n-6) ratio is important in the maintenance of an appropriate level of biological membrane fluidity, which is in turn, essential for ion channel function, membrane receptor activity and the release of neurohormones, i.e. the signaling processes of every cell. Numerous neurotransmission pathways have been found to be dysfunctional in schizophrenia, which raises the probability that membrane phospholipids that modulate the activity of both receptors and are involved in signal transduction may be part of the etiology of schizophrenia.

PUFA metabolism disturbances have repeatedly been described in patients with schizophrenia. Deficiencies of PUFA were described in red blood cell (RBC) membranes of patients with schizophrenia [3-6]. PUFA RBC concentration is known to reflect its concentration in the brain in adult humans [7]. Disturbances in PUFA metabolism have been shown to exist even at early stages of schizophrenia prior to initiation of antipsychotic therapy [3] and in individuals at ultra-high risk of psychosis [8]. A recent meta-analysis confirms the presence of n-3 and omega-6 (n-6) PUFA abnormalities in antipsychotic-naive, antipsychotic-free schizophrenia patients and in patients currently treated with antipsychotics [9]. Post-mortem brain studies have revealed decreased levels of PUFA, especially docosahexaenoic acid and arachidonic acid, in the frontal lobes of schizophrenia patients. PUFA deficiencies in neuronal membranes can be the result of the increased release of PUFA from membrane phospholipids, or its decreased incorporation within them. Both processes were found to be defective in schizophrenia patients.

Since PUFA cannot be effectively synthesized in humans, decreased incorporation may be the result of dietary deficiencies. One of our recent studies identified differences in declared PUFA consumption between UHR individuals who converted to full-threshold psychosis and who did not develop psychotic disorder (article submitted for publication). Differences were also found in declared PUFA consumption between healthy controls (HC), UHR individuals and patients with first-episode schizophrenia (FES). The PUFA consumption patterns of UHR individuals were comparable with those of FES patients and were significantly different from HC subjects: UHR and FES groups declared significantly higher consumption of omega-6 fatty acids than the HC group.

### Membrane phospholipids hypothesis of schizophrenia

The repeated observation of lipid metabolism dysfunctions in patients with schizophrenia led to the formulation of the Membrane Phospholipid Hypothesis of Schizophrenia by David Horrobin [10], according to which, cellular PUFA abnormalities can lead to schizophrenia in susceptible individuals. A number of pathophysiological changes observed in schizophrenia can be related to PUFA metabolism: eg. decreased membrane fluidity [11], altered monoaminergic neurotransmission [12-14], production of proinflammatory cytokines, increased oxidative stress damage to the neuronal membrane and reduced anti-oxidative defense [15]. PUFA depletion in schizophrenia can be a result of increased phospholipase A2 activity and oxidative damage, which together lead to increased release of PUFA from neuronal membranes [16]. Phospholipase A2 (PLA2) gene polymorphisms have been associated with susceptibility to schizophrenia [17,18] and antipsychotic medications have been found to decrease PLA2 expression in patients with schizophrenia [19]. Another mechanism influencing PUFA levels in the cell membranes of schizophrenia patients is decreased incorporation of PUFA into membrane phospholipids due to lipoprotein lipase dysfunction and inadequate synthesis of long-chain PUFA from their essential precursors: linoleic acid (LA) for n-6 PUFA and alpha-linolenic acid (ALA) for n-3 PUFA [20].

### Efficacy of n-3 PUFA in schizophrenia

#### Supplementation studies in schizophrenia

Observations of PUFA metabolism dysfunctions in schizophrenia patients at different stages of disease together as well as those with PUFA dietary deficiencies prompted intervention trials. Seven randomized controlled trials (RCTs) comparing n − 3 PUFA eicosapentaenoic acid (EPA) with placebo as supplemental treatment to antipsychotics in schizophrenia have been reported. Two of these studies report that EPA had a positive effect on primary efficacy [21,22], and all but one [23] of the others reported at least some beneficial effect on secondary outcomes [21,24-26]. One study on 80 first-episode patients over 12 weeks found EPA to decrease time to response in patients with non-affective psychosis, and showed a 20% reduction in antipsychotic use in the EPA augmented group [26]. A recent meta-analysis of RCTs revealed no beneficial effect of EPA augmentation on symptom severity in schizophrenia. However, no conclusion could be drawn regarding the medium- to long-term effects of EPA in schizophrenia, particularly regarding relapse prevention in the early course of psychotic disorders [27]. Moreover, a 12-week RCT conducted in individuals at high clinical risk of schizophrenia provides preliminary evidence that intervention composed of 1.2 g of PUFA (i.e. EPA + DHA) could prevent transition to first-episode psychosis.

Supplementation with n-3 PUFA may demonstrate higher efficacy in populations of individuals at high-risk of psychosis and early psychosis than in patients with chronic schizophrenia. A recent study notes that PUFA metabolism disturbances are present relatively early in the course of schizophrenia and diminish over time as the disease progresses, and that treatment with antipsychotic medications (aripiprazole and risperidone) was able to correct aberrant PUFA levels in first-episode schizophrenia patients, but not in a group of patients with chronic schizophrenia [28]. This suggests that intervention with n-3 PUFA can be more effective when administered early in the course of disease.

### PUFA and the reduced risk of such adverse effects as tardive dyskinesia and metabolic side effects associated with antipsychotics

A growing body of evidence suggests that n-3 PUFA may play a role in reducing the intensity of adverse effects associated with antipsychotics. Antipsychotic-induced dyslipidemia was successfully treated with n-3 PUFA supplementation [29]. Short term (6 weeks) n-3 supplementation was able to modulate cardiometabolic risk factors in patients treated with olanzapine and either valproate or lithium [30]. Berger et al. report that ethyl-EPA supplementation used as add-on therapy in patients with schizophrenia was associated with a 20% reduction in the use of antipsychotics, reduced percentage of patients experiencing the extrapyramidal side effects, constipation and the sexual side effects of antipsychotic therapy [26]. Additionally, n-3 PUFA supplementation has been shown to play a possible role in reducing the risk of tardive dyskinesia [22], however, these observations are not consistent [25]. Reduction of motor side effects of antipsychotics have also been observed in animal models [31-33]. Reduction in the intensity of side effects associated with n-3 supplementation can increase adherence to antipsychotics and in turn, influence the severity of symptoms and the relapse rate in first episode schizophrenia.

### Relapse in schizophrenia

#### Relapse in schizophrenia

It is estimated that up to 90% of individuals developing first-episode schizophrenia achieve remission from symptoms in the first 12 months of therapy [34] but recovery defined as attainment of both functional and symptomatic remission for 2 years [35] is achieved in only 10-20% of patients [36]. This is partly because a great number of patients will experience a relapse of psychotic episodes during the first years following diagnosis. Longitudinal studies find that about one third of patients will have experienced a relapse before 1 year after recovery, and two thirds before 2 years [37,38]. Seventy to eighty percent of patients experience relapse within three to five years [39]. There is some evidence that with recurring episodes of psychosis, the time to obtain response increases and the proportion of patients achieving remission diminishes [40]. Psychotic relapse and incomplete recovery can lead to the chronic phase of the disease. Neurodegeneration and deterioration occurs mainly in the first 5–10 years of illness. The long-term outcome of the disease may be associated with the number of relapses and the quality of remission achieved [40]. These observations have generated increased interest in relapse prevention in schizophrenia and have prompted repeated attempts to understand the risk factors responsible for recurrence of the psychotic exacerbation.

#### Relapse risk factors

A systematic review based on a meta-analysis of clinical trials revealed that the risk of relapse in schizophrenia decreases with antipsychotic medication use [41], and the main risk factor for relapse is antipsychotic therapy discontinuation [38,40]. The main reason for antipsychotic non-adherence are safety and tolerability issues, as well as lack of insight associated with psychosis. Although second generation antipsychotics are frequently used in treatment of patients diagnosed with schizophrenia, they are associated with a high risk of adverse cardiometabolic effects such as weight gain, glucose intolerance and diabetes, and lipid profile abnormalities. A recent study has found that both duration of relapse and the intensity of treatment with antipsychotics may be associated with brain volume loss [42]. Andreasen et al. found that the duration of relapse was closely related to loss of brain tissue over time in multiple brain regions, including total cerebral volume loss, as well as loss in subregions, particularly the frontal lobes. They report that relapse duration and treatment intensity both contribute to brain tissue loss, but while treatment effects are more diffusely distributed, the relapse effects are most strongly associated with changes to the frontal lobe tissue. The authors conclude that relapse prevention should be sustained using the lowest possible medication dosages to control the symptoms.

#### n-3 PUFA in relapse prevention

To date, only one study of the use of n-3 PUFA in relapse prevention has been reported. Emsley et al. recently published the results of a study assessing the efficacy of intervention composed of 1 g of DHA and 2 g of EPA plus 300 mg of the antioxidant alpha-liopic acid (LA) or placebo in patients diagnosed with schizophrenia, schizoaffective disorder or schizophreniform disorder meeting the criteria of relapse in whom antipsychotic therapy was tapered and discontinued according to the current guidelines. The study was terminated prematurely due to the severity of some of the relapse episodes, as well as the high relapse rates in both treatment groups: 90% and 75% in active and placebo groups respectively. The authors did not observe significant differences in relapse rates between the study arms. The study concludes that n-3 PUFAs + alpha-LA does not appear to be a suitable alternative to maintenance antipsychotic treatment in relapse prevention. The authors argue that on the basis of their findings, the current treatment guidelines suggesting antipsychotic discontinuation 2–3 years after the first psychotic episode should be revised [43].

### Rationale for the study

Hence, there is a growing body of evidence based on animal models, *in vitro* and observational studies, as well as from randomized clinical trials, which suggests that n-3 PUFA plays a role in the pathophysiology of schizophrenia, and that supplementation with these essential compounds may be worth consideration, especially at early stages of the disorder. N-3 PUFA supplementation was found to be effective in reducing the risk of transition into psychosis in individuals at ultra-high risk of psychotic disorders. Data from basic studies indicates that PUFA metabolism impairments are present at early stages of schizophrenia. However, meta-analyses of RCTs do not indicate that n-3 PUFA may be efficacious in reducing the severity of symptoms in chronic schizophrenia patients: antipsychotic medications are still the mainstay of schizophrenia therapy.

The number of schizophrenia patients treated with antipsychotic polypharmacotherapy is increasing [44], despite there being insufficient evidence from well-designed clinical trials and in spite of accumulating data implicating several serious adverse effects and increased health costs associated with antipsychotic polytherapy [45]. Despite increasing antipsychotic usage, more than 80% of patients experience relapse within the first 5 years following the first psychotic episode and the majority of deterioration takes place during the first few years after diagnosis. Unplanned antipsychotic discontinuation was shown to be the main risk factor for relapse in schizophrenia [40]. However, Andreasen et al. report brain volume loss to be associated not only with the duration of psychosis, including relapses, but also with the intensity of antipsychotic utilization [42]. Hence, it is particularly important that the smallest possible doses of antipsychotics are used to reduce the duration of psychotic episodes in schizophrenia, including relapses. To this end, n-3 supplementation was shown to be safe and well tolerated [46], and can allow reduced doses of antipsychotic medications to be used to achieve and sustain remission in schizophrenia [26].

Most previous studies assess the short-term efficacy of n-3 fatty acids in the exacerbation of chronic schizophrenia, but few of them have been conducted in a population of first-episode schizophrenia patients. The intervention period was 8 weeks in the majority of studies. It is well established that the period needed to refill the n-3 fatty acid store in the human body, and hence to achieve maximum metabolic effects, is about 3–4 months. Most studies assess an intervention composed of only EPA, one study compared EPA and DHA in two separate study arms and only one study used a mixture of EPA + DHA. The only study that reports an intervention composed of EPA + DHA was conducted in ultra-high risk patients.

It is important to underline that most reported studies were carried out in chronic schizophrenia patients, while only two of them supplemented first-episode patients. Moreover, the majority of the RCTs conducted so far are based on ethyl-eicosapentaenoic acid (ethyl-EPA) and most interventions were short term, i.e. 8–12 weeks. DHA is an important constituent of neuronal membranes, which have an important role in brain development and function. The DHA molecule itself has unique structural properties that appear to provide optimal conditions for a wide range of cell membrane functions. Its presence in the neuronal membranes provides a biochemical and biophysical basis for membrane fluidity and neurotransmission. In addition, it was recently found to be a source of two important endogenous neuroprotective compounds: protectins and resovlins.

One rudimentary source of DHA is marine algae, but it can be found in a concentrated form in fish and marine oils. Mammalian cells lack the specific enzymes required for the *de novo* synthesis of alpha-linolenic acid (ALA), the precursor for all n-3 fatty acid syntheses. The endogenous synthesis of DHA from ALA in humans is much more limited than previously assumed, and low consumption of fish and marine oils can lead to DHA deficiencies. In addition, the excessive consumption of omega-6 fatty acids in the modern Western diet further displaces DHA from membrane phospholipids. An emerging body of research suggests that DHA plays a unique role in neurodevelopment [47,48] and the prevention of neuropsychiatric [49] and neurodegenerative disorders [50,51].

Hence, it is planned to conduct a long-term randomized, placebo-controlled, single site study of a EPA + DHA intervention in first-episode schizophrenia patients. The efficacy of EPA + DHA added-on to antipsychotics in reducing psychopathology and the relapse rate in early schizophrenia have not yet been studied systematically. The OFFER study aims to systematically evaluate the long-term efficacy of n-3 PUFA in reducing psychopathology and preventing relapse in patients with first-episode schizophrenia.

### Main research questions and hypotheses

The following research questions were formulated:Is supplementation with n-3 fatty acids added to antipsychotic medications an efficacious intervention for patients in the acute phase of first-episode schizophrenia?Can add-on therapy with n-3 fatty acids initiated in the acute phase of disease be efficacious in reducing the one-year relapse rate in first-episode schizophrenia.Is add-on therapy with n-3 PUFA related to changes in cognitive performance of first-episode schizophrenia patients?What are the biochemical and structural brain correlates of n-3 PUFA add-on therapy in first-episode schizophrenia patients? Specifically, are oxidative stress and defense as well as brain plasticity mechanisms involved? Is add-on n-3 PUFA supplementation associated with structural brain changes concerning gray and white matter, such as cortical thickness and fiber density, axonal diameter or myelination?

## Methods

### Study design

The study will be based on a randomized, double-blind, placebo-controlled, parallel-group single-center augmentation trial (RCT) of either 2.2 g per day of n-3 PUFA, or olive oil placebo, added on to an adjustable dose of antipsychotic medication. The background antipsychotic therapy will be chosen and titrated according to the Polish standards of pharmacotherapy of mental disorders [52]. The use of benzodiazepines (diazepam, lorazepam, alprazolam, clonazepam), chlorprothixene, zuclopenthixol acetate will be allowed if control of behavioral symptoms is indicated. Zolpidem and zopiclone will be used in patients complaining of insomnia. For patients presenting significant depressive symptoms the use of selective serotonin reuptake inhibitors will be allowed. For all participants, the protocol allows for treatment of emergent extrapiramidal side effects with biperiden and treatment of akathisia with propranolol, lorazepam, or clonazepam. Using PUFA supplements other than contained in study medication will not be permitted throughout the study.

### Participant sample

The intended study population is composed of inpatients admitted to the Psychiatric Clinics of the Central Teaching Hospital, Medical University of Lodz. Patients will be enrolled consecutively as they are admitted to the hospital. Eligible patients will be (1) aged 16–35, (2) diagnosed with first-episode schizophrenia according to the International Classification of Diseases 10th version (ICD-10), which is an obligatory classification of mental disorders in Poland, (3) currently psychotic as reflected by the presence of at least one psychotic symptom daily for more than one week (delusions, hallucinations, disorders of thought form other than simple acceleration or retardation, and disorganized, bizarre, or markedly inappropriate behavior). Diagnosis will be confirmed by the mini neuropsychiatric interview plus (MINI plus) [53]. Patients will be excluded if more than two years have passed since the onset of positive symptoms, if the patient have bleeding disorders, or have been taking fish oil supplements or anticoagulants for any reason, were diagnosed with drug-induced psychosis, first-episode mania or organic disorders presenting with psychotic symptoms, if the patient has a history of intellectual disability, or a history of head injury with loss of consciousness, or any acute or unstable medical condition.

The trial procedures will be explained verbally and in writing to all eligible patients. All participants will provide written informed consent prior to study enrollment. The study will be conducted in accordance with the Declaration of Helsinki and the study protocol has been approved by the Ethics Committee of the Medical University of Lodz.

### Power calculation

Previous studies have suggested medium effect sizes in favor of n-3 fatty acids [21,22]. On the basis of previous studies, we assume that there will be a nontrivial correlation between baseline and outcome scores at follow-up, and it is hypothesized that baseline scores will explain 25% of the variation in outcome measures. Power calculation revealed that 36 participants per study arm will result in 80% power to detect medium effect size (0.3) at a significance level of 0.05 (two sided). Assuming an attrition rate of 15%, we aim to enroll 82 patients.

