The analysis of covariance (ANCOVA) with intervention type as term and baseline PANSS score as covariate will be used to assess the change from baseline in PANSS scores to week 8 and 26 separately. If the overall ANCOVA of the baseline-to-endpoint change score will be significant, pairwise comparison will be performed using Dunnett t test. Analyzes will be two-sided for both ANCOVA and Dunnett test with the type I error rate for rejecting null hypothesis set at 0.05. The same analyses will be repeated to assess the significance of differences in changes of CDSS, CGI and GAF scores between the study arms.

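### The power statement leaves the metric of its 0.3 unnamed: 36 per arm has 80% power only for a difference of about 0.6 SD, and 82 enrolled with 15% attrition leaves about 70, not 72

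*Protocol article*

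**What the plan says.** The sample-size basis for the primary outcome is one short paragraph, Power calculation, in the protocol article.

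- Effect, size and power: "36 participants per study arm will result in 80% power to detect medium effect size (0.3) at a significance level of 0.05", with the test stated to be two-sided.
- Covariate gain: "it is hypothesized that baseline scores will explain 25% of the variation in outcome measures".
- Enrolment: "Assuming an attrition rate of 15%, we aim to enroll 82 patients".

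Under Statistical methods and analytic plan, Primary aim, the planned test is "The analysis of covariance (ANCOVA) with intervention type as term and baseline PANSS score as covariate", applied to the change in PANSS at weeks 8 and 26 separately. The Secondary aim section confirms equal arms of 41. The paragraph does not say whether 0.3 is a standardised mean difference (Cohen's d), Cohen's f or a correlation, and it gives no target in PANSS points and no SD.

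**The concern.** In a two-arm comparison of mean change, many readers will take an effect size of 0.3 as a difference of 0.3 SD. With 36 per arm that is far from 80% power. Other readings meet 80%, but only because the same 0.3 then means a difference about twice as large. A reader cannot tell which was meant, and the label medium does not settle it, because the usual medium value depends on the metric.

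What is at stake is how a null result is read. The article itself reports a meta-analysis with no benefit on symptom severity (Efficacy of n-3 PUFA in schizophrenia) and a first-episode trial without sustained symptomatic benefit, possibly because of a ceiling effect (Rationale for intervention arms). If this trial is also null, the paragraph invites the claim that a medium effect was excluded with 80% sensitivity. For d = 0.5 that would not be true.

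The enrolment figure is a second, separate matter: it does not deliver the 72 patients that the same paragraph asks for.

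**Working it through.** **Inputs, all from the protocol article.** n = 36 per arm; two-sided alpha 0.05; baseline R² = 0.25; two-group ANCOVA with one covariate; attrition 15%; 82 enrolled, 41 per arm.

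**Formula.** Baseline adjustment shrinks the residual SD by √(1 − 0.25) = 0.866. For a difference of d (in unadjusted SD units), the noncentrality is d/0.866 × √(n/2), with 2n − 3 degrees of freedom. With n = 36, √(36/2) = 4.243, df = 69, and the two-sided critical t is 1.995. For two equal groups d = 2f. A simple correlation r between group and outcome converts as d = 2r/√(1 − r²).

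**Attempt to reproduce 80% at 36 per arm**

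| Reading of 0.3 | d | Noncentrality | Power at 36 per arm | Per arm for 80% |
|---|---|---|---|---|
| Standardised mean difference | 0.30 | 1.470 | 30.5% | 132 |
| Cohen's f | 0.60 | 2.939 | 82.6% | 34 |
| Simple correlation | 0.629 | 3.081 | 86.0% | 31 |
| For comparison: usual medium, d = 0.5 or f = 0.25 | 0.50 | 2.449 | 67.6% | 49 |

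A normal approximation gives nearly the same power: 31.2%, 83.6%, 86.9% and 68.8%. Reading 0.3 as a partial correlation, given baseline, yields 74.9%, and 80% then needs 82 in total.

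None of these returns 36 per arm at 80%. Among the variants tried, f = 0.3 with a one-sided 0.05 test and no gain from the covariate does return exactly 72 in total (power 80.9%). It contradicts both the stated two-sided test and the stated 25%.

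**Difference detectable with 80% power at R² = 0.25**

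- 36 per arm: d = 0.580
- 35 per arm: d = 0.588, which is f = 0.588/2 = 0.294

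**Attrition**

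- Expected to remain: 82 × 0.85 = 69.7, against 2 × 36 = 72.
- Needed: 72/0.85 = 84.7, so 85, or 86 in equal arms.
- The stated 41 per arm matches 36 × 1.15 = 41.4 rounded down. That is a plausible origin, not one the article states.

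**Power at 35 per arm.** d = 0.3: 29.8%. d = 0.5: 66.3%. d = 0.6: 81.5%.

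**In PANSS points, on an assumed SD.** The article gives no SD. If it were 15 to 20 points, the detectable difference at 36 per arm would be 0.58 × 15 = 8.7 to 0.58 × 20 = 11.6 points, against 4.5 to 6 points for d = 0.3.

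**The case against.** The strongest reply is that Cohen's f is a common metric for ANCOVA, which is the planned test. On that reading 36 per arm gives about 83%, the 80% target is met, and nothing is wrong with the power figure. A simple correlation of 0.3 also clears 80%, and 0.3 is the conventional medium value for a correlation, so even the label can be defended under that convention. This stands. A reader might infer that the 80% is simply false and that true power is 31%. The article does not support that, because it never calls 0.3 a standardised mean difference; the 31% is conditional on that reading.

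What the reply does not remove is that the metric is unstated, and that every reading reaching 80% implies a difference of about 0.6 SD. On the scale of mean differences that is above the usual medium.

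A second reply is that the attrition slip is trivial. That also largely stands: on the f reading, 35 per arm still has about 81.5% power. The primary analysis moreover keeps patients with at least one efficacy evaluation on day seven or later and uses multiple imputation, so 70 is the number expected with observed outcomes, not the analysis set. Imputation does not rescue the other readings, however. Even with all 41 per arm fully observed, power is 34% for d = 0.3 and 73% for d = 0.5.

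Finally, calling 0.6 SD optimistic would be a judgement. The article rests its effect size on two earlier trials whose results are not shown here.

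**Conclusion.** The paragraph needs correcting, but the defect is one of definition and consistency, not a demonstrated failure of power.

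1. The effect-size metric is unnamed, and no reading that uses all the stated inputs returns 36 per arm at 80%.
2. Whatever was meant, the design has 80% power only for a standardised difference of about 0.58 (36 per arm) to 0.59 (35 per arm). For d = 0.5 it has about 66 to 68%, and for d = 0.3 about 30 to 31%.
3. Enrolment of 82 falls two or three short of the 84.7 implied by 72 completers at 15% attrition, or four short in equal arms. The effect on power is about one percentage point.

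These results rest on the article's own R² of 0.25, equal arms and a two-sided 0.05 test. Only the PANSS-point figures need an outside assumption, the SD. A reader might conclude that the sample must be enlarged. The documents do not force that, since 82 is adequate for a 0.6 SD target if that is what was intended.

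**What to change.** Keep N = 82 and restate the paragraph along these lines:

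> 82 randomised, 15% attrition, about 70 with observed outcomes (35 per arm), baseline R² = 0.25, two-sided 0.05: 80% power for a standardised mean difference of about 0.59 (Cohen's f about 0.29), 66% for d = 0.5 and 30% for d = 0.3.

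Name the metric and use the standardised difference in place of the word medium. Add that a null result would not exclude d = 0.5 with 80% sensitivity. If the sponsor has a PANSS SD, give the target in points as well and state where the SD comes from.

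The cost is wording only: no extra patients and no change to design or analysis. The stated sensitivity becomes less favourable. If the sponsor would rather keep 72 observed completers as the basis, enrolment must be 85, or 86 in equal arms.
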